#### Study procedures

##### Core biopsy (standard treatment)

Percutaneous renal core biopsy will be performed directly before the IRE procedure, utilizing the procedural anaesthesia. A minimum of two percutaneous core biopsies will be harvested for pathological examination. In the Academic Medical Center Amsterdam all patients presented with a renal mass on cross-sectional imaging, suspicious for malignancy, are advised to undergo renal core biopsies.

##### IRE ablation (study intervention)

This study utilizes the Angiodynamics (Queensbury, New York) NanoKnife™ IRE device (Figure 2A), also registered as the HVP-01 Electroporation System. This IRE system consists of a Low Energy Direct Current (LEDC) generator, footswitch and 19G monopolar needle electrodes (15 or 25 cm length). The device and electrodes have been developed for soft tissue ablation. Both the device and the electrodes carry a CE certificate for cell membrane electroporation. The system has been approved by the FDA via 510(k) Premarket Notifications (K060054, K080202, K080376, K080287). All 510(k) cleared components are indicated for surgical ablation of soft tissue.

**Figure 2 Fig2:**
[figure not shown]
**IRE equipment.** The NanoKnife IRE console **(A)** utilizes 19G monopolar needle electrodes **(B)** which can be locked together using external spacers **(C)**.

The IRE procedure will take place at the Radiology department CT-room under general anaesthesia with muscle relaxation, as described by Nielsen et al. [25]. An interventional radiologist accompanied by a urological surgeon will perform the procedure. ECG monitoring and synchronization of IRE pulses will be performed under anaesthetic supervision. Needle electrodes (Figure 2B) will be placed under ultrasound and CT guidance using external spacers (Figure 2C) for fixation during pulse administration. Probe number and placement will be adjusted for specific tumour size or targeted tissue ablation in case of clinical tumor stage ≥ cT1b. Currently practiced IRE settings for tumour ablation are electrode spacing of 15 mm, electrode tip exposure of 15 mm, 90 pulses of 90 μs (synchronised with ECG) and a pulse intensity of 1500 V/cm. The IRE treatment cycle will take 5–10 minutes; total operating time is estimated at 90 minutes. If deemed clinically fit, patients will be discharged 24 hours after the IRE procedure. Post procedural pain will be quantified at 4 hours, 24 hours and 1 week by means of VAS score, cumulative opiate use and patient satisfaction.

##### CEUS and MRI imaging (study intervention)

CEUS and MRI imaging will take place at baseline, one week and four weeks after IRE ablation in order to assess lesion size and enhancement. Furthermore, this will reveal possible complications and any unexpected abnormalities as a result of the IRE procedure that may affect the final surgery (radical nephrectomy).

Contrast enhanced ultrasound (CEUS) utilizes a contrast agent to increase echogenicity of blood for better visualisation tissue vascularisation. Ultrasound contrast contains 3–5 μm microbubbles surrounded by a phospholipid shell. Early studies have shown promising results for the use of CEUS in the follow-up after cryoablation [26]. This study uses a Philips iU22 (Philips Healthcare, Bothell, USA) ultrasound device which is optimised for contrast studies, in combination with SonoVue (Bracco, Milan, Italy) a third generation ultrasound contrast agent with a elimination half-life of 6 min [27].

MRI will be performed using a Siemens Avanto 1.5 Tesla MRI scanner (Siemens Healthcare, Erlangen, Germany) with a 16-channel body array coil. The MRI protocol will include at least the following sequences: T2-trufi with fat suppression, T1-fl2d contrast enhanced in and out of phase, T2-haste, T1 vibe unenhanced and dynamic series at 30 seconds, 60 seconds, and 15 minutes. As MRI contrast agent Gadovist 1.0 (Bayer Pharma, Leverkusen, Germany) will be used.

##### Radical nephrectomy (standard treatment)

Radical nephrectomy will be performed four weeks after renal IRE ablation, either open or laparoscopic depending on patient specific factors such as co-morbidities and tumour characteristics. It will be performed according to department protocol by two experienced urologic surgeons.

#### Sample size

This is a phase 2A (IDEAL), pilot study. In ablation of renal masses, location and size of the renal mass influence treatment variables: number of probes and device settings. The sample size of 10 patients was chosen in order to explore 2–3 probe configurations. In this phase of research, this requires at least 3 repetitions of a specific probe configuration in order to assess consistency and the potential influence of other factors (tumor location, tissue composition) on ablation volume. Furthermore, a recently published animal study by Sommer et al. demonstrated a successful evaluation of CT imaging versus histological analysis with 3 probe configurations using a sample size of 10 cases [28]. A sample size of 10 patients, testing 2–3 IRE probe configurations, does not allow for reliable statistical analysis. We will therefore confine our results to averages and standard deviations of the assessed volumetric data.

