### Study design

This is a prospective, human, in-vivo study among 10 patients presenting with a solid renal mass, and candidates for radical nephrectomy (RN). A study flowchart is provided in Figure 1. Prior to the IRE procedure baseline MRI and CEUS imaging will be acquired. Subsequently the patients will undergo IRE ablation of their renal mass. Follow-up at one and four weeks post IRE will be performed using MRI and CEUS imaging. At these time points procedure and device related adverse events (AE) will be registered using the Common Terminology Criteria for Adverse Events (CTCAE) version 4.0 guideline. Four weeks after IRE the patients will undergo radical nephrectomy after which pathological examination will be performed to evaluate IRE ablation success. Core biopsies are harvested before IRE ablation in order to assure tumour differentiation in case of complete ablation. Correlation between pathology and imaging will reveal the efficacy of MRI and CEUS for the assessment of IRE lesions.

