**Study design flowchart.**

### Study objectives

Primary objectives:To determine the efficacy of IRE ablation of renal masses, measured by pathological examination of the targeted tumour.To determine the safety of IRE ablation of renal masses, by evaluating device and procedural adverse events using CTCAE v4.0.

Secondary objectives:To evaluate the efficacy of MRI in the imaging of ablation success, the extent of the ablation zone, one and four weeks post IRE ablation.To evaluate the efficacy of CEUS in the imaging of ablation success, the extent of the ablation zone, one and four weeks post IRE ablation.

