## Discussion

Before progressing to follow-up studies of IRE in renal masses it is vital to perform tissue specific testing of IRE ablation efficacy and safety. This trial will investigate IRE ablation efficacy by comparing 3D histopathological examination of a (partially) resolved IRE lesion, through radical nephrectomy with 1) examination of 3D imaging using MRI and CEUS and 2) 3D prediction of ablation volume as given by the manufacturer. IRE ablation volume and shape is influenced by many variables such as needle number, needle configuration, and device/pulse settings. With only 10 IRE ablations it is not within in the scope of this study to experiment with a wide variety of IRE settings. We aim to test 2 needle electrode configurations, while keeping the device settings constant. In clinical practice contrast enhanced CT scanning is most widely used modality for follow-up after renal mass treatment. In this study however it was decided not to investigate CT imaging in order to limit the cumulative radiation exposure. Study participants are already receiving an estimated 32 mSv of ionizing radiation due to the CT guided IRE procedure. Adding CT follow-up to the research protocol would result in 2–3 additional 4 phase CT scans, besides any CT scans that are necessary after the final treatment. Another limitation of this study is the follow-up period, which is limited at 4 weeks. Animal trials have shown renal IRE lesions to be partially resolved at 3–4 weeks [20-22]. Preferably radical nephrectomy would be postponed longer than 4 weeks, giving the IRE lesion more time to mature, allowing for better analysis of intermediate ablation results. However, further prolonging the final treatment is unethical at this early phase of the research. A final limitation is the tumour size. Patients who are candidate for radical nephrectomy, except for patients with ERDS, will have tumours larger than 4 cm. Ablative therapies are indicated for tumours ≤ 4 cm, which means that we not testing renal IRE in the intended population. The choice for radical nephrectomy was made out of the concern that IRE ablation might complicate a subsequent partial nephrectomy leading to impaired surgical outcome. In our opinion this trial will provide essential knowledge on IRE of renal masses, guiding future research of this promising ablative technique.

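### The rule limiting results to averages and SDs of volumes leaves adverse events, viability findings and the paired imaging comparison without a planned result

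*Protocol article*

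**What the plan says.** The Sample size section of the protocol article gives the reason and then the rule: "A sample size of 10 patients, testing 2–3 IRE probe configurations, does not allow for reliable statistical analysis", followed by "We will therefore confine our results to averages and standard deviations of the assessed volumetric data". No exception is made for outcomes that are not volumes.

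The Study objectives section names two primary objectives:
- efficacy: "To determine the efficacy of IRE ablation of renal masses, measured by pathological examination of the targeted tumour"
- safety: "To determine the safety of IRE ablation of renal masses, by evaluating device and procedural adverse events using CTCAE v4.0"

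The secondary objectives concern how well MRI and CEUS show the ablation result at one and four weeks. On these, the Study design section says: "Correlation between pathology and imaging will reveal the efficacy of MRI and CEUS for the assessment of IRE lesions". The Background makes the same promise and adds the manufacturer's predicted volume as a second comparator for the histology.

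The Analysis section lists what is collected. Pathology covers ablation volume, but also viability staining, viable cells in the ablated zone, skip lesions and damage to vessels, collecting system and pelvis. The radiologist reads residual tumour and skip lesions as well as volume. For CEUS, only basic measurements are described.

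**The concern.** The reporting rule is narrower than the questions the trial sets itself.

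- **Safety.** An adverse event is not a volume. Followed literally, the rule gives this co-primary objective no result.
- **Efficacy.** Ablated volume is one pathology item. A mean volume does not say in how many patients viable cells remained in the zone meant to be destroyed, which the stains are there to show.
- **Imaging and prediction.** The trial measures the same lesion by several methods in the same patient. A mean and SD for each method discards that pairing, so the reader cannot tell how far a scan is off in an individual.

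At stake is whether a trial that offers participants no benefit and adds risk can report on its own objectives. The Abstract expects essential knowledge on safety and efficacy from it.

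**Working it through.** **1. The plan's own figure.** The size is justified by configurations and repetitions: "The sample size of 10 patients was chosen in order to explore 2–3 probe configurations", and "this requires at least 3 repetitions of a specific probe configuration in order to assess consistency". Three configurations × 3 repetitions = 9, which 10 covers. Two configurations × 3 = 6, and 10 allows 5 each. The figure is coherent, but it is built on consistency of ablation volume, not on what ten patients can say about adverse events or viability. (The Discussion says "We aim to test 2 needle electrode configurations, while keeping the device settings constant". The two statements should be reconciled, because results will be displayed by configuration.)

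**2. Objectives against the rule.**

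| Question | Data collected | Covered by averages and SDs of volumes? |
|---|---|---|
| Safety | CTCAE adverse events | No |
| Efficacy, extent | Histological volume | Yes |
| Efficacy, viability | Viable cells, skip lesions | No |
| Imaging, extent | MRI volume, CEUS measurements | Only per method, unless differences are meant |
| Imaging, residual tumour | Radiologist's reading | No |

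**3. Means and SDs do not determine agreement.** Take two methods with equal means and a common SD *s*, and let *r* be the within-patient correlation. Then

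SD of differences = *s*·√(2(1 − *r*)); 95% limits of agreement = ±1.96 × that SD.

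The article gives no volume SD, so *s* = 6 cm³ is an assumption. Everything scales with *s*.

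| *r* | Limits in units of *s* | Limits at *s* = 6 cm³ |
|---|---|---|
| 1 | 0 | 0 |
| 0.9 | ±0.88 | ±5.3 cm³ |
| 0.5 | ±1.96 | ±11.8 cm³ |
| 0 | ±2.77 | ±16.6 cm³ |

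For example, at *r* = 0.9: 6 × √0.2 = 2.68, and 1.96 × 2.68 = 5.3. At *r* = 0: 6 × √2 = 8.49, and 1.96 × 8.49 = 16.6. The reported output (two means, two SDs) is identical in every row.

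**4. What ten patients can support.** Exact (Clopper-Pearson) two-sided 95% intervals:
- 0/10: upper limit 1 − 0.025^(1/10) = 30.8%
- 1/10: 0.3% to 44.5%
- 8/10: 44.4% to 97.5%
- 10/10: lower limit 0.025^(1/10) = 69.2%

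The chance of seeing at least one patient with an event is 1 − 0.9¹⁰ = 65% if the true risk is 10%, and 1 − 0.8¹⁰ = 89% if it is 20%.

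For ten paired differences (t with 9 df = 2.262), the 95% CI half-width is
- mean difference: 2.262/√10 = 0.72 SD of differences
- each limit of agreement: 2.262 × √(1/10 + 1.96²/18) = 1.27 SD of differences.

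These are imprecise but reportable. An SD of volumes from the same ten patients, or from three per configuration, is also a small-sample estimate, so the rule does not favour the more reliable quantity.

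**The case against.** The strongest reply is that the sentence is being read too literally. It closes a paragraph about consistency of ablation volume and may mean only that volumes will be described rather than tested. The article registers adverse events, stains for viability, scores pain and gives a monitoring board safety and efficacy data, so the authors can hardly intend to report none of it. This is plausible, but the sentence does not say it. The data collection is sound; the fault is in the stated reporting rule. Nor is this detail left to an unseen analysis plan, since the article states the restriction itself.

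Other parts of the reply stand, and they rule out stronger readings that a reader might infer:
- *That the rule answers neither primary objective.* Too strong for efficacy. Histological volume is a listed pathology item, and the Background ties efficacy to the comparison with imaging and predicted volume.
- *That volumes will be pooled over configurations.* The article never says so, and planned repetitions per configuration suggest otherwise.
- *That a correlation coefficient is planned.* None is named, and the Discussion describes the same task as a comparison.
- *That averages and SDs of paired differences are excluded.* They are not. They would describe agreement, so the objection on pairing holds only if the summaries are per method.
- *That complete tumour ablation is the goal in every patient.* The section on IRE ablation foresees ablation of a target region in tumours of stage cT1b or above.

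**Conclusion.** The point holds as a fault in a stated rule. As written, the Sample size section provides no result for the co-primary safety objective, omits the viability and skip-lesion part of efficacy, and, if averages and SDs are given per method, cannot show within-patient agreement with histology. The reason given does not support the restriction: ten patients are too few for useful hypothesis tests, but not for counts, exact intervals or ten displayed pairs.

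On size, the safety gap is complete under the literal reading. For agreement, the same planned output is compatible with limits anywhere from 0 to ±2.77 SD over correlations from 1 to 0; the cm³ figures rest on the assumed SD of 6, equal SDs and equal means. The exact intervals assume one yes/no outcome per patient and all ten patients evaluable.

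**What to change.** In the Sample size section, limit the restriction to hypothesis testing and state that the trial will report:

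1. **Efficacy:** the number of patients with no viable cells in the targeted zone (not the whole tumour where only targeted ablation is planned), with an exact 95% CI, alongside the volume summaries.
2. **Safety:** the number of patients with any device- or procedure-related adverse event, and the number by CTCAE grade, with exact 95% CIs.
3. **Imaging and prediction:** individual within-patient differences (or ratios) from histology, for predicted volume, MRI and CEUS separately.
   - The four-week scan is the main comparison, because histology is obtained at four weeks; the one-week scan is shown separately.
   - All pairs are displayed by probe configuration, with the mean difference and SD of differences. Limits of agreement serve only as imprecise description.
   - CEUS is compared on the measurements actually taken.

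State in the Background and Study design sections that correlation means this paired comparison, not a correlation coefficient; a method that always read half the true volume would have a coefficient of 1. The cost is a little more analysis and visibly wide intervals. No new data are needed.

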#### Potential benefits and risks

There are no benefits for patients that participate in this study. Study participants will be exposed to additional risk when compared to standard treatment. They will have to undergo an additional procedure under general anaesthesia with muscle relaxation. An independent expert, assigned by the IRB, has estimated the exposure to ionizing radiation during the IRE procedure at 32 mSv.

IRE is a new tissue ablation technology and IRE of renal tumours has only been tested in a limited number of patients. It might be that certain risks and side effects are unforeseen at this point in time. Potential risks associated with IRE for renal tumours, using the NanoKnife™ system, are listed in Table 2. In addition, it is not expected that renal IRE in patients with ERDS will result in an acute dependence on dialysis. Both animal and human studies did not show a substantial decrease in GFR following renal IRE ablation. Research among patients suffering from renal insufficiency has however not yet been conducted. Therefore the possibility of a decrease in renal function leading to the need for dialysis cannot be completely excluded.

**Table 2 Tab2:** **Potential risks associated with IRE of renal tumours**

Potential hazards of renal IRE ablation	Potential effects
Excessive energy delivery	Muscle contraction, burn, damage to critical anatomical structure, unintended tissue ablated, bradycardia/hypotension, vagal stimulation/asystole, electrical shock, myocardial infarction, stroke, death
Insufficient/no energy delivery	Ineffective ablation, no ablation
Unintended mains or patient circuit voltage exposure to patient or user	Electrical shock
Incorrect timing of pulse delivery	Transient arrhythmia, prolonged arrhythmia, stroke, death
Unintended interference with implanted devices containing electronics or metal parts	Myocardial infarction, stroke, death
Unexpected movement of the device and displacement of the electrodes	Hypotension, damage to critical anatomical structure, pneumothorax, mechanical perforation, haemorrhage, unintended tissue ablated, electrical shock, death
Sterile barrier breach	Infection, sepsis

#### Data safety monitoring board

The study will be monitored by a data safety monitoring board (DSMB) consisting of an independent urologist and a statistician. This team will monitor patient safety and treatment efficacy data during the study. Monitoring procedures are predetermined and described in the DSMB charter, approved by the IRB of the Academic Medical Center, Amsterdam. Additional DSMB meetings can be called at any time if deemed necessary by the DSMB or the Principal Investigator.

#### Analysis

The NanoKnife console provides 2D images displaying a cross section of the predicted ablation zone perpendicular to the needle tract. Using the AMIRA software package (FEI Visualisation Sciences Group, Burlington, USA) the 2D ablation zone cross sections will be stacked along the length of the exposed electrode tip providing predicted:3D reconstructionablation zone shape/symmetryablation zone volume (cm^3^)

Pathological examination of the resected specimen will be performed by an experienced genitourinary pathologist. Prior to the study specific pathology protocol, sufficient material is acquired for routine renal tumour examination. The kidneys will be cut in a coronal plane creating 3–4 mm slices. After macroscopic inspection, the whole IRE lesion will be excised and embedded for sectioning and staining. Stains to be used will include hematoxylin and eosin (H&E), nicotinamide adenine dinucleotide (NADH) diaphorase and terminal deoxynucleotidyl transferase dUTP nick end labelling (TUNEL). NADH staining confirms cell viability and TUNEL staining conversely indicates cell non-viability. Combining the results of these stains will provide a detailed analysis of cell viability within the IRE ablation zone.

Microscopic examination will assess:IRE ablation volume (cm^3^)ablation zone shape/symmetrytransition zoneviable cells within ablation zoneskip lesionsdamage to blood vesselsdamage to the collecting systemdamage to the renal pelvis

The pathology slides will be digitized using a Ventana iScan HT pathology slide scanner (Roche, Tuscon, USA). A 2D reconstruction of the segmented tumour will be constructed using Fiji (ImageJ). Within the 2D reconstruction the ablation zone will be outlined. Using the AMIRA software package the 2D tumour sections will be stacked to render a 3D reconstruction of the histopathology. This reconstruction is used to assess the exact lesion volume and shape.

MRI and CEUS imaging will be analysed by a specialised urologic radiologist focussing on:ablation volume (cm^3^)ablation zone shape/symmetryresidual tumour on ablation zone borderskip lesions within ablation zonetransition zone between ablated and normal renal tissuedamage to vital structures

Within the CEUS images basic measurements will be performed. Within in the MRI images the ablation zone and the kidney as a whole will be outlined. Using the AMIRA software package the outlined MRI images will be stacked to render a 3D reconstruction of the kidney and the IRE ablation zone within.

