Before progressing to a long-term IRE follow-up study it is vital to have pathological confirmation of the efficacy of the technique. Furthermore, follow-up of IRE ablation requires an accurate imaging modality. This trial will investigate IRE ablation efficacy by correlating 3D histopathology of a resected IRE lesion with: 1) 3D reconstructed imaging using MRI and contrast enhance ultrasound (CEUS), and 2) the 3D predicted ablation volume as provided by the manufacturer. The objectives of the study are assessing the safety and efficacy of IRE of renal masses (primary objectives), and assessing the efficacy of MRI and CEUS for the initial evaluation and short-term (4 weeks) follow-up of IRE lesions (secondary objectives). This study conforms to the recommendations of the IDEAL Collaboration and can be categorised as a phase 2A development trial [24].

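### The histological ablation volume is called exact and used as the reference for MRI, CEUS and the predicted zone, but it comes from embedded tissue with no described fresh measurement or rescaling

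*Protocol article*

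**What the plan says.** The Analysis section of the protocol article gives one sequence for the resected kidney. It starts with gross cutting: "The kidneys will be cut in a coronal plane creating 3–4 mm slices". Next comes "After macroscopic inspection, the whole IRE lesion will be excised and embedded for sectioning and staining". The sections are stained and the slides digitised, the ablation zone is outlined in a 2D reconstruction, and "Using the AMIRA software package the 2D tumour sections will be stacked to render a 3D reconstruction of the histopathology". The stated purpose is plain: "This reconstruction is used to assess the exact lesion volume and shape". Ablation volume in cm³ is listed among the items of the microscopic examination, so it is assigned to processed sections and not to the fresh slices.

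The Background states how the volume is used: "This trial will investigate IRE ablation efficacy by correlating 3D histopathology of a resected IRE lesion with" reconstructed MRI and CEUS on the one hand, and the manufacturer's predicted ablation volume on the other. The Discussion repeats both comparisons. The Sample size section says that ten patients do not support reliable statistical analysis and limits reporting to means and SDs of the volumetric data.

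**The concern.** MRI and CEUS measure the lesion in the living kidney, and the predicted zone is likewise expressed in the dimensions of the tissue as treated. The histological volume is measured on tissue that has been excised, embedded and sectioned. If that processing shrinks the tissue, the two sides of the comparison are on different scales and the reference is the smaller one.

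Error from slice spacing or hand outlining can fall either way and may partly cancel across patients. Shrinkage acts in one direction. If it is roughly uniform, it multiplies every histological volume by the same factor k. The mean becomes k × mean and the SD becomes k × SD, so the coefficient of variation is unchanged. The reported spread would give no sign of the problem, and more patients would not reduce it.

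Two wrong conclusions are possible. Accurate imaging or planning software could be reported as overestimating the ablation. Conversely, imaging or a prediction that is truly too small could appear to agree with histology. Both bear on the imaging objectives and on how well the planned zone predicts the achieved one, and the means and SDs of these volumes are the only statistics the article plans.

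**Working it through.** **Check against a stated figure.** The article gives no fixation, embedding or shrinkage figure, so there is no number of the plan's to reproduce. What can be calculated is the sensitivity of the volume to shrinkage.

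**Inputs.**
- From the Analysis section: coronal slices 3–4 mm thick; volume obtained by stacking outlined sections.
- Assumed, not in the documents: linear shrinkage s of 0, 5, 10, 15 or 20%.
- Assumed for illustration: MRI or the prediction equals the true in-vivo volume exactly.

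**Formulas.**
- In-plane case: section contours shrink in two directions, but sections are stacked at the spacing of the fresh slices. Histological / true volume = (1 − s)².
- Three-axis case: the stacking distance shrinks as well. Histological / true volume = (1 − s)³.
- Apparent overestimation by an accurate comparator = 1 / ratio.

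**Results.**

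| Linear shrinkage s | (1 − s)² | Volume loss | Accurate comparator appears | (1 − s)³ | Volume loss | Accurate comparator appears |
|---|---|---|---|---|---|---|
| 0% | 1.000 | 0% | 1.00× | 1.000 | 0% | 1.00× |
| 5% | 0.9025 | 9.8% | 1.11× | 0.857 | 14.3% | 1.17× |
| 10% | 0.810 | 19.0% | 1.23× | 0.729 | 27.1% | 1.37× |
| 15% | 0.7225 | 27.8% | 1.38× | 0.614 | 38.6% | 1.63× |
| 20% | 0.640 | 36.0% | 1.56× | 0.512 | 48.8% | 1.95× |

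Example at s = 10%, in-plane: 0.90² = 0.81, a loss of 19%, and 1 / 0.81 = 1.23.

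**The reverse error.** With s = 10% in-plane, a comparator that truly captures only 81% of the lesion gives 0.81 / 0.81 = 1.00 against histology. A real 19% underestimate would be reported as perfect agreement.

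**Which column applies.** Stacking at the 3–4 mm cutting interval gives the in-plane column. The article does not state the stacking distance, so the three-axis column is an upper case that needs that further assumption.

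**The case against.** **The article is condensed.** It refers to a study-specific pathology protocol that is not shown, and scaling details may be there. Macroscopic inspection precedes embedding, and measurement at that step is neither described nor excluded, so it would be wrong to infer that nothing is measured before embedding. This stands as a caution. It does not remove the point, because the article does more than stay silent: it assigns volume to the microscopic examination, derives it from stacked slides and calls the result exact.

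**The sizes are assumed.** This also stands. The documents support no particular shrinkage value, and at zero shrinkage there is no bias. But without a fresh measurement the trial could not show which row of the table applies.

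**The comparison is already confounded by healing.** The Background reports cortical shrinkage at 28 days in animals, and the Discussion accepts that the lesion may have partly resolved by nephrectomy. A histological volume below the predicted zone can therefore be biological, and a processing correction will not change that. This stands for the comparison with the prediction. It has less force for the four-week MRI, which is taken at about the time of the nephrectomy.

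**Nothing is tested.** No agreement threshold exists for shrinkage to overturn. That limits the consequence to the reported means and SDs, but those are the planned results.

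**A stronger reading that the documents do not support.** A reader might infer that embedding the whole lesion destroys the enzyme activity behind the NADH stain, so that surviving tumour reads as dead and the primary efficacy result is biased towards complete ablation. The article says "NADH staining confirms cell viability and TUNEL staining conversely indicates cell non-viability", and the primary efficacy objective is pathological. But it names no fixative and no embedding medium, and frozen embedding is compatible with its wording. What is missing is laboratory detail that such an article commonly leaves to the pathology protocol. Nor does viability rest on NADH alone: "Combining the results of these stains will provide a detailed analysis of cell viability within the IRE ablation zone". No error in the viability reading can be shown.

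**Conclusion.** The point holds for volume only. The article presents a volume from embedded sections as exact and uses it as the reference for in-vivo imaging and for the predicted zone, without describing a fresh measurement or a rescaling. Any processing shrinkage would make that reference too small. For assumed linear shrinkage of 5–15%, the shortfall is 10–28% with sections stacked at fresh slice spacing, and 14–39% if all three axes shrink.

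The direction follows from the method; the size rests wholly on the assumed shrinkage and on how the sections are stacked. The point does not touch the viability reading and does not separate processing shrinkage from lesion resolution by four weeks. It is a correctable weakness of the measurement and does not invalidate the trial. It merits a change before tissue is processed, because fresh dimensions cannot be recovered afterwards.

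**What to change.** In the Analysis section:

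1. At macroscopic inspection, photograph each fresh slice with a scale bar, outline the lesion where it is visible, and record the slice thickness.
2. Rescale the digitised slide contours to the fresh slice dimensions, and stack them at the recorded thickness, before the AMIRA volume is computed. Recording thickness also settles the 3–4 mm range, whose ends differ by 4 / 3 = 1.33 in stacked volume.
3. Describe the result as shrinkage-corrected instead of exact, and report the scaling factor per patient beside the means and SDs.
4. Say in the limitations that lesion resolution by four weeks remains uncorrected.

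The cost is minor: photography and measurement on tissue already resected, plus some image-registration work. Patient care does not change, and whole-lesion sampling for the stains stays as planned. There is no reason here to confine NADH to selected strips, which would reduce viability sampling for the primary reading.
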